#### Sample size

Based on the result from our previous study, a clinically meaningful change from baseline in PMR was assumed to be − 0.15 in both the 2 g/day and the 4 g/day LC n-3 PUFA groups, and no change in the no-treatment group, with a common standard deviation of 0.2 among the groups. The sample size per group of 46 archives 90% power to detect the assumed difference in changes, using a two-group, one-sided *t* test of 1.25% significance level, where the overall significance level of the one-sided test for the two comparisons (i.e., the 2 g/day group versus the no-treatment group, and the 4 g/day LC n-3 PUFA group versus the no-treatment group) was 2.5% and the Bonferroni adjustment was applied to control the Type I error rate. Allowing for adjustment of withdrawals, missing data or loss to follow-up, 50 subjects per group will be recruited into the trial.

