#### Statistical methods

All the analysis will be made on an intent-to-treat (ITT) basis. The 2 g/day and the 4 g/day EPA/DHA groups will be compared against the no-treatment group for all primary analysis. For the primary outcome, treatment effects between the groups and their 95% confidence intervals are calculated from analysis of covariance (ANCOVA) models with adjustment for baseline values of the outcome measure. To confirm the conclusion from ITT-based analysis, the same analysis is repeated on a per-protocol set (PPS), where criteria for determining the PPS assignment would be established and confirmed by the Steering Committee. For secondary and other outcomes, we will use the chi-squared test for binary outcomes, and a *t* test for continuous outcomes. For subgroup analyses, we will use regression methods with appropriate interaction terms (respective subgroup × treatment group). Multivariable analyses will be based on logistic regression for binary outcomes and linear regression for continuous outcomes. We will examine the residual to assess model assumptions and goodness-of-fit.

All *p* values will be reported to four decimal places with *p* values less than 0.001 reported as *p* < 0.001. Up-to-date versions of SAS (SAS Institute, Cary, NC, USA) will be used to conduct analyses. For all tests, we will use two-sided *p* values with an alpha ≤ 0.05 level of significance

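### The two-sided 0.05 rule in Statistical methods, taken literally, does not carry through the Bonferroni level on which the two primary comparisons were sized

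*Protocol article*

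**What the plan says.** The protocol article gives a significance rule in two places.

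- **Sample size.** There are two comparisons, each dose against no treatment. The calculation uses a one-sided "test of 1.25% significance level, where the overall significance level of the one-sided test for the two comparisons", and the section adds that this overall level "was 2.5% and the Bonferroni adjustment was applied to control the Type I error rate". A change of −0.15 is assumed "in both the 2 g/day and the 4 g/day LC n-3 PUFA groups, and no change in the no-treatment group"; the SD is taken to be 0.2 in every arm. This leads to 46 per group for 90% power, raised to 50 to allow for losses.
- **Statistical methods.** "The 2 g/day and the 4 g/day EPA/DHA groups will be compared against the no-treatment group for all primary analysis". The section continues: "For the primary outcome, treatment effects between the groups and their 95% confidence intervals are calculated from analysis of covariance (ANCOVA) models", adjusted for baseline. It closes with one rule for all tests: two-sided "values with an alpha ≤ 0.05 level of significance". It makes no exception for the primary outcome and mentions neither Bonferroni nor any other multiplicity procedure.

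**The concern.** Both sections set a level for the same two tests, and the levels differ. The move from one-sided to two-sided is not the difficulty, because one-sided 1.25% and two-sided 2.5% have the same critical value in the favourable direction. The difficulty is the level per comparison: two-sided 0.025 in Sample size, and two-sided 0.05 in Statistical methods if its closing sentence is applied as written.

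What is at stake is the success criterion of the primary endpoint. If one dose gave a two-sided p of 0.04 against no treatment, an analyst following Statistical methods would report a significant effect and one following Sample size would not. Each could cite the protocol, and the choice would be made after the results are seen.

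**Working it through.** **Inputs.** From Sample size: difference 0.15, SD 0.2, 46 per group, one-sided 1.25% per comparison, overall one-sided 2.5%. From Study design: allocation 1:1:1. From Statistical methods: two-sided 0.05 and 95% intervals.

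**1. Reproduce the plan's sample size.** Two-sample t test:

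- Standard error of the difference = 0.2 × √(2/46) = 0.0417
- Noncentrality = 0.15 / 0.0417 = 3.60, with 90 degrees of freedom

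| Level per comparison | n per group | Power |
|---|---|---|
| one-sided 1.25% (= two-sided 2.5%) | 45 | 89.7% |
| one-sided 1.25% (= two-sided 2.5%) | 46 | **90.4%** |
| two-sided 5% | 38 | 89.7% |
| two-sided 5% | 39 | 90.5% |
| two-sided 5% | 46 | 94.5% |

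The stated 46 is the smallest n with 90% power at the Bonferroni level. At two-sided 0.05 per comparison, 39 would be enough. The trial was therefore sized on the rule in Sample size, not on a literal reading of Statistical methods.

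**2. Family-wise error under each rule.** With equal arms and a shared control, the two test statistics have correlation (σ²/n) / (2σ²/n) = 0.5. With both null hypotheses true and c the critical value, the family-wise error is 1 − P(|Z₁| ≤ c, |Z₂| ≤ c) for a bivariate normal with correlation 0.5. The error in the favourable direction is 1 − P(Z₁ ≤ c, Z₂ ≤ c).

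| Rule per comparison | c | Two-sided | Favourable direction |
|---|---|---|---|
| two-sided 0.05 | 1.960 | **9.07%** | **4.54%** |
| two-sided 0.025 (Bonferroni) | 2.241 | 4.65% | 2.32% |
| intended ceiling | | 5% | 2.5% |

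A simulation with pooled variance at 46 per group gave 9.0% and 4.5% for the first rule, and 4.6% and 2.3% for the second.

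**3. Where the two rules disagree.** On the p value scale the disputed zone is 0.025 to 0.05, whatever model is used. On the PMR scale, for the t test used in the sample size:

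- two-sided 0.05: 1.987 × 0.0417 = 0.083
- two-sided 0.025: 2.280 × 0.0417 = 0.095

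Observed reductions between 0.083 and 0.095 would get opposite verdicts. These limits belong to the unadjusted t test and would shift under the planned ANCOVA. As an illustration, suppose that 0.2 is the SD of change and that change correlates with baseline at r (r is assumed; the protocol gives none). Both limits are then multiplied by √(1 − r²): to about 0.079–0.091 at r = 0.3 and 0.059–0.068 at r = 0.7. The zone moves and narrows but does not close.

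**The case against.** The strongest reply is that the sections can be reconciled. An overall one-sided 2.5% corresponds to an overall two-sided 5%, so the 0.05 in Statistical methods could be the overall level, with Bonferroni dividing it as Sample size describes. Statistical methods omits the adjustment but does not withdraw it. This reading is possible and shows what was probably intended. It is not what the section says, though: the sentence covers all tests, sets no primary comparison apart and does not call 0.05 an overall level.

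A reader might infer that the trial has no multiplicity control at all. That goes too far, because Sample size names the comparisons, the overall level and the method. What is missing is the link to the analysis.

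The 95% intervals are supporting evidence only. The protocol does not make them the decision rule, and conventional intervals are often shown beside adjusted tests.

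A reader might also extend the point to the many secondary and other endpoints tested at 0.05. The document does not support that. The Bonferroni rule was never said to cover them, so nothing is contradicted, and their multiplicity policy may properly sit in a statistical analysis plan that is not shown.

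Two arguments about weight remain. The Background calls the study exploratory; but Study design calls it a superiority trial, and Sample size commits to Type I error control. And under the assumed effect the rules disagree in only about 4% of results per comparison (94.5% − 90.4% = 4.1 percentage points). That is true, but the issue is the error rate when there is no effect. Nor does a possible separate analysis plan answer the point, because it concerns two statements in this document, not something left out.

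**Conclusion.** The point holds for the two primary comparisons. If Statistical methods is followed as written, the chance of at least one false positive primary result is about 9.1% two-sided, or 4.5% in the favourable direction, against intended ceilings of 5% and 2.5%. This rests on equal arms, a shared control, approximate normality and both nulls being true. Without using the correlation, the Bonferroni bound is 10% two-sided. The stated sample size is correct for the stricter rule. Because the conflict concerns how primary success is declared, it should be settled before the results are seen.

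**What to change.** In Statistical methods, state that each of the two primary ANCOVA comparisons against no treatment is tested at two-sided 0.025 (Bonferroni, overall two-sided 0.05) and reported with a 97.5% confidence interval. Limit the two-sided 0.05 sentence to the other tests. Dunnett's procedure on the same ANCOVA is an acceptable alternative: with correlation 0.5 it corresponds to a nominal two-sided level of about 0.027 per comparison. If it is chosen, Sample size should name it too.

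The cost is wording only. The 46 per group, and so the 50 to be recruited, are unchanged, with 90.4% power per comparison by the planned t test. The primary intervals become about 15% wider (2.280 / 1.987 = 1.15).

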### Study organization

The research group consists of researchers and statisticians at the National Cerebral and Cardiovascular Center, Suita, Japan and an independent data monitoring committee.

#### Monitoring

Adverse events (AE) will be collected during the study periods. At each study visit, the principal investigator or investigator will interview the subject about whether any subjective symptoms have occurred. When an AE occurs, the principal investigator or investigator must promptly take appropriate measures and follow up all subjects experiencing an AE until the symptoms resolve, or any clinically significant abnormal laboratory values have returned to the baseline values. All AEs will be documented in the CRF. The Data Monitoring Committee is independent of the investigators. No interim analysis is planned.

#### Definition of AEs

An AE is defined as any untoward medical occurrence in a subject administered a drug; it does not necessarily have to have a causal relationship with this treatment. An AE can, therefore, be any unfavorable or unintended sign (including a clinically significant laboratory abnormality), symptom, or disease temporally associated with the use of a drug whether or not it is considered related to the drug.

#### Reporting of AEs

When an AE occurs, the principal investigator or investigator must promptly take appropriate measures and follow up all subjects experiencing an AE until the symptoms resolve, or any clinically significant abnormal laboratory values have returned to baseline values, the addition to, or switching of, the investigational product, or there is a satisfactory explanation for the change (for AEs that are permanent or irreversible), regardless of whether the causal relationship of the AE with the investigational product. All AEs will be documented in the CRF. The following information will be documented for each AE: event term; dates of onset and disappearance; frequency; severity; causal relationship between the event and the investigational product (not related or related); action taken for the investigational product; outcome of event; and seriousness. For AEs that are considered to be unrelated to the investigational product, the reason for ruling out the causality should be documented in the comment column of the CRF.

## Discussion

Although the results of many randomized controlled trials using statins have shown the usefulness of LDL-cholesterol-lowering therapy, the extent of coronary artery disease suppression did not exceed approximately 30% [27]. However, optimal management of residual risk following statin therapy is now emerging.

The LC n-3 PUFAs, especially EPA and DHA, exert pleiotropic cardiometabolic effects with a diverse range of actions. The LC n-3 PUFAs can ultimately reduce blood pressure, reduce platelet aggregation, and improve arterial and endothelial function. Importantly, LC n-3 PUFAs do not have a major effect on fasting total cholesterol and LDL-cholesterol levels; they effectively reduces triglyceride and remnant lipoprotein in hyperlipidemic patients [28]. Those effects of LC n-3 PUFAs are beneficial for the cardiovascular system. The present AQUAMARINE-EPA/DHA study is expected to clarify the effect of LC n-3 PUFAs on high-risk coronary plaques.

In the AQUAMARINE pilot study, we found that statin treatment reduces the PMR of coronary HIPs and that the reduction of PMR reflects improvement of high-risk features of HIPs under statin treatment. However, in many plaques, high PMR values remain (PMR > 1.0) even after statin treatment [25]. These results suggest that PMR measured by CMR can be useful not only to evaluate high-risk coronary plaques but also to assess coronary residual risks after statin treatment.

Therefore, this trial will provide novel insights into the effect of EPA/DHA therapy on residual risk in patients with CAD who are taking appropriate statin therapy.

### Trial status

Period of patient recruitment: recruitment started in August 2015.

## Abbreviations

AA: Arachidonic acid
CAD: Coronary artery disease
CMR: Cardiac magnetic resonance
CRF: Case Report Form
CTA: Computed tomography angiography
DHA: Docosahexaenoic acid
EPA: Eicosapentaenoic acid
HDL: High-density lipoprotein
HIP: High-intensity plaque
LC n-3 PUFA: Long-chain n-3 polyunsaturated fatty acid
LDL: Low-density lipoprotein
LPL: Lipoprotein lipase
PCI: Percutaneous coronary intervention
PMR: Plaque-to-myocardium signal intensity ratio
T1WI: T1-weighted imaging
VLDL: Very-low-density lipoprotein
